## Abstract

The length of hospital stay following cardiac surgery remains a significant challenge. Enhanced recovery protocols, alongside the use of health applications, offer promising potential for safely and effectively reducing postoperative length of stay. The *Registro Paulista de Cirurgia Cardiovascular* III (REPLICCAR III) study, registered at Clinicaltrials.gov (NCT06786819), aimed to investigate the impact of an optimization application integrated within an optimized recovery-based protocol on postoperative hospitalization duration in patients undergoing Coronary Artery Bypass Graft Surgery (CABG) in the state of São Paulo.

## Introduction

Advances in cardiac surgery, driven by large databases, risk scoring systems, and technical innovations, have been significant [1–3]. However, the length of postoperative hospital stay remains a persistent challenge, especially within the Brazilian Unified Health System, where the average stay for coronary artery bypass graft (CABG) surgeries is approximately 11.8 days [4]. This issue is exacerbated by the lack of patient-centered protocols and misalignment within care teams [5–7].

Protocols based on the Enhanced Recovery After Cardiac Surgery (ERACS) concept aim to optimize care processes through a multidisciplinary, evidence-based approach, seeking to reduce both metabolic and psychological stress while fostering patient engagement in the recovery process [1,5,8]. Although promising, its implementation faces challenges related to management and adherence [9,10].

Digital platforms have shown potential to optimize outcomes by enhancing communication among healthcare teams and allowing better monitoring of care processes, thereby supporting adherence to protocol metrics [11–14]. These platforms have also demonstrated positive impacts on the patient and family education [15–17]. Within the context of rapid recovery, Schlund et al. [18] published a study on the use of a mobile application for patients undergoing elective colorectal surgery under the Enhanced Recovery After Surgery (ERAS) program, observing greater adherence to medication and shorter hospital stay, consistent with findings from other studies [19,20]. With the increasing use of mobile devices, health applications emerge as a promising means of promoting and facilitating health education.

In this context, the *Registro Paulista de Cirurgia Cardiovascular* III (REPLICCAR III) study seeks to analyze the impact of integrating a process customized application within enhanced recovery care pathways based on the concept of optimized recovery on postoperative hospitalization for patients undergoing CABG in the state of São Paulo, through the stepped-wedge cluster randomized design.

## Methods

A prospective, multicenter, randomized study using the stepped-wedge cluster design to analyze the impact of an application integrating an optimized recovery pathway, compared with standard care, on postoperative length of stay in patients undergoing CABG across five reference hospitals in the state of São Paulo. Patient recruitment and data collection began on 10 March 2025 (version 1, N = 252) and are expected to continue for one year to reach the target sample size. Therefore, the study is currently in the recruitment and data collection phase (Fig 1). It is registered at Clinicaltrials.gov (NCT06786819).

**Fig 1 pone.0338301.g001:**
[figure not shown]
Schedule of enrollment, interventions, and assessments of REPLICCAR III project activities. Based on SPIRIT guidelines and recommendations [21,22]. Circle indicates training and implementation period, Arrow indicates continuous delivery of intervention. REPLICCAR III: Registro Paulista de Cirurgia Cardiovascular III; PREM: Patient-reported experience measures; PROM: Patient-reported outcome measures; CABG: Coronary artery bypass grafting.

Participation in the study required approval from the executive board of each hospital to ensure that multiprofessional teams strictly adhere to the established protocols in the intervention group. A project representative at each participating institution will be responsible for obtaining informed consent, overseeing the patient’s perioperative course, and issuing quarterly progress reports to the coordinating center. The coordinating institution will monitor protocol adherence (in real time using the app) and ensure accurate data collection at each participating center monthly and through quarterly audits.

Fig 2 shows the study flowchart and timeline of project activities.

**Fig 2 pone.0338301.g002:**
[figure not shown]
Study flowchart and timeline of REPLICCAR III project activities. REPLICCAR III: Registro Paulista de Cirurgia Cardiovascular III.

The Standard Protocol Items: Recommendations for Interventional Trials (SPIRIT 2025 Checklist) [21,22] is provided in figure in S1 File.

### Randomization design

Randomization of hospitals/reference centers (clusters) will be performed at the beginning of the project. Allocation will be carried out by an independent statistician and kept confidential by the study coordinating center. Hospitals will be informed of their assignment to the intervention group one month before the training of their multidisciplinary teams on the application incorporating the study protocols.

Each cluster will be randomly assigned to the intervention group in a staggered fashion:

**Control period:** While the hospital is not randomized to the intervention group, data will be collected from the “control” period, consisting of observational data from standard care practices.**Implementation and training period:** Data from this period will not be analyzed, as it serves as an adaptation phase. Training on the application and optimized recovery protocols will be carried out through classes, meetings, and training sessions (with support from the STRATUS Center for Medical Simulation, Brigham Health) to ensure correct system use and adherence to the care protocol, using the intervention of *Tempos Certos* Protocol [23], based on Enhanced Recovery After Cardiac Surgery (ERACS) [24] concepts adapted to the context of the Brazilian Unified Health System.**Intervention period:** After the implementation period, collected data will be assigned to each hospital’s “intervention” group. As the project progresses, periodic meetings will be held to address challenges and provide updates on care at each institution.

### Follow-up

All patients included in the analysis will be followed up at 30 days and 6 months post-discharge, via telephone call, to assess hospital readmission rates, morbidity, patient-reported experience measures (PREM) [25,26], patient-reported outcome measures (PROM) adapted from the model by Ben-Ali et al. [27], as outlined in fil Table in S2 Table, and mortality.

Variables from the PREM and PROM instruments are collected in electronic forms dedicated to the REPLICCAR III project in REDCap, via telephone interviews conducted by the study’s technical research trainee and trained undergraduate research students [28]. All personnel were trained and instructed by the coordinating center to perform these activities, under the supervision of each responsible investigator. To mitigate loss to follow-up, several strategies were implemented, including providing patients with informational leaflets alongside the informed consent form and before hospital discharge, with follow-up call schedules and the names of study personnel. Information is reinforced to patients and their relatives during hospitalization.

An independent adverse event committee will follow up patients to track and report any adverse events and evaluate their potential relationship to the study design.

### Data storage and intervention application

All data will be securely stored online on dedicated, user-friendly platforms developed for the REPLICCAR III project in Cardux, REDCap, and Kamay. Both data storage and intervention platforms comply with the Brazilian General Data Protection Law (LGPD – Law no. 13.709/2018) [29], which regulates the processing of personal data in Brazil, protecting the fundamental rights to freedom and privacy for study participants and healthcare professionals using the platforms.

A confidentiality agreement will govern data use, ensuring alignment with the study objectives. The study will be conducted and monitored by an independent committee formed for data management and storage. All authors are required to sign a commitment statement affirming the accuracy of the collected data and adherence to the study protocol, although reviews and comments may be submitted throughout the study.

### Database

The Cardux platform (https://cardux.net/, Fig 3) and REDCap [30] will be used for secure data storage, accessible by username and password for both study phases. Variables collected during the study will be based on insights from the REPLICCAR II project [31], addressing data related to patient demographics (e.g., gender, age, comorbidities), pre-, intra- and postoperative phases (e.g., clinical exam results, use of cardiopulmonary bypass, need for blood transfusion, complications), as well as hospitalization metrics (e.g., length of surgical procedure, postoperative intubation time, length of hospital stay). In addition, follow-up data will be collected at 30 days and 6 months post-discharge, including variables such as need for readmission, further interventions, incidence of acute myocardial infarction, mortality, and variables related to PREM and PROM analysis.

**Fig 3 pone.0338301.g003:**
[figure not shown]
Cardux database REPLICCAR III dashboard.

### Intervention application

Prior to the intervention phase, participating hospitals will complete a one-month training period to familiarize their staff with the platform and the *Tempos Certos* pathway, based on Enhanced Recovery After Cardiac Surgery [23]. The Kamay application (https://www.projetokamay.com.br/) will be used only during the intervention period, associated by Cardux database, with access protected by usernames and passwords, for real-time process monitoring.

Patients will be introduced to the Kamay application and assisted with downloading and accessing it by the REPLICCAR study group at each site during recruitment. Additionally, every patient will receive an informational pamphlet (Fig 4) containing step-by-step instructions for downloading and using the application.

**Fig 4 pone.0338301.g004:**
[figure not shown]
Pamphlet provided to intervention patients.

The application comprises three modules:

Education of patients and families

This module provides a user-friendly educational content in text, image and video formats, personalized for the REPLICCAR study, aiming to enhance patient and family engagement while reinforcing prehabilitation and postoperative rehabilitation guidelines (Fig 5). It includes features for scheduling messages to patients’ mobile devices at predefined dates and times, as well as tracking interaction and engagement levels. Patients can be grouped by specific parameters, such as smoking, activity level, or waiting time for surgery, enabling targeted content delivery. The module also supports surveys and facilitates communication between patients and healthcare staff. As patients progress through hospitalization stages (preoperative ward, operating room, ICU, postoperative ward, hospital discharge), their families receive real-time updates.

**Fig 5 pone.0338301.g005:**
[figure not shown]
Educational module of the application for patients and families.

Communication among the multiprofessional team

Facilitates coordinated communication among multidisciplinary team members regarding patients enrolled in the project pathway, including scheduling and tracking of each process step (Fig 6). This module records real-time completion of activities, monitors time spent at each stage, and ensures adherence to protocol activities.

**Fig 6 pone.0338301.g006:**
[figure not shown]
Multiprofessional care coordination team module of the application.

Activity management via Dashboard

An interface that enables monitoring of key metrics such as time spent per stage, adherence to activities, and patient survey results, among other indicators (Fig 7).

**Fig 7 pone.0338301.g007:**
[figure not shown]
Application dashboard for monitoring activities and metrics.

The patient application monitors access to educational content, while the healthcare professionals’ application tracks clinical team compliance (Fig 7).

### Study population

Inclusion criteria: patients aged ≥18 years; indication for primary isolated CABG, either elective or urgent; ownership of a personal cell phone with internet access and proficiency in its use; ability to understand and fully agree to the informed consent form.

Exclusion criteria: patients requiring concurrent surgical procedures; glycosylated hemoglobin level >8%; creatinine clearance 4%; physical or mental disabilities preventing protocol adherence; and patient or family refusal to participate.

### Ethical approval and informed consent

This study was approved by the Ethics Committee for Analysis of Research Projects (CAPPesq) at Hospital das Clínicas da Universidade de São Paulo, under approval number 77933424.8.1001.0068. Written informed consent will be obtained from all patients included in the study, regardless of the analysis period.

### Statistical analysis

Variables will be compared using the chi-square test, Student’s t-test, or Kruskal-Wallis test. Categorical variables will be presented as numbers and percentages, while continuous variables will be presented as mean ± standard deviation (SD) or median and interquartile range (IQR). All analyses will be conducted using R software version 3.1.2 [32], within an integrated development environment for statistical computing and graphics, available in precompiled binary versions for Windows. Given the stepped-wedge cluster randomized design and the potential intra-cluster correlation, mixed effect models will be applied to evaluate possible cluster and period effects.

The randomization sequence for the five clusters (participating hospitals) will be computer-generated. Allocation will be hidden at both the cluster and patient levels, with prior knowledge limited to the project leader and the team responsible for sequence generation. Blinding will be maintained for the analysis of results.

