### Sample size calculation

Based on the postoperative length of stay found by Da Silva et al. [33], with a mean of 8.34 days (SD ± 10.32) and targeting a mean length of stay of 5.56 days (SD ± 10.32) after intervention, the sample calculation of REPLICCAR III was made using a two-tailed t-test for differences between two independent means. With a significance level of 5%, test power of 80%, and effect size of 0.27, the required sample size was determined to be 436 patients. Accounting for a 10% potential loss to follow-up, a final target sample size is 480 patients (240 per group). Sample size calculation was performed using G*Power software, version 3.1.9.4.

Because REPLICCAR III uses a stepped-wedge cluster randomized design, we incorporate the intra-cluster correlation (ICC), cluster size variability, and period effects (1 period = 2 months, time).

Design and allocation

We plan a cross-sectional stepped-wedge cluster randomized design 5 clusters (hospitals, K), 6 periods that includes the control phase (T), and an average of 16 patients per cluster-period (m), totaling K × T × m = 5 × 6 × 16 = 480 patients. All models will include fixed period effects to adjust for secular trends across time.

Correlation and cluster size variability.

Based on pilot information and published data on postoperative length-of-stay within hospitals, we assume a very low ICC = 0.001 and balanced recruitment across clusters (coefficient of variation of cluster sizes CV ≈ 0, achieved through monitoring and capped enrollment).

$$DE=\left[1+\left(m-1\right)\times ICC\right]\times \left(1+CV^{2}\right)$$

Under these assumptions, the standard design effect is:

DE≈1+15×0.001×=1.015(withCV≈0)

Therefore, with ICC = 0.001, CV ≈ 0, K = 5, T = 6, and m = 16, we will recruit N = 480 patients.

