### Outcomes

The primary outcome is the difference in postoperative length of stay between the intervention and control groups. Secondary outcomes include adherence to protocol metrics during the intervention period; comparison of morbidity, mortality rates, hospital readmissions, and assessment of PROMs and PREMs between the intervention and control group at 30 days and up to 6 months after CABG.

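### The plan names only unadjusted tests for comparing and never says that the intervention effect comes from the planned mixed model, so a time-confounded primary comparison remains open

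*Protocol article*

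**What the plan says.** Three sections of the Protocol article bear on how the groups are compared.

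- **Statistical analysis.** The only sentence about comparing is "Variables will be compared using the chi-square test, Student’s t-test, or Kruskal-Wallis test". It names no outcome and is not limited to baseline or descriptive variables. Later in the same paragraph, with the stepped-wedge design and intra-cluster correlation given as reasons, it says that "mixed effect models will be applied to evaluate possible cluster and period effects".
- **Sample size calculation.** The patient number starts from a "two-tailed t-test for differences between two independent means". Under the design heading it adds: "All models will include fixed period effects to adjust for secular trends across time".
- **Outcomes.** "The primary outcome is the difference in postoperative length of stay between the intervention and control groups". Morbidity, mortality and readmission are also to be compared between the groups, with PROMs and PREMs assessed between them.

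No sentence links the intervention-control difference in stay, or any secondary contrast, to the treatment term of a mixed model. No sentence calls the simple tests descriptive.

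**The concern.** In a stepped wedge every hospital starts in control and ends in intervention, so intervention patients are systematically later. A chi-square, t or Kruskal-Wallis test cannot carry a period term. Applied to the two groups, it counts any change in stay over the trial year as part of the intervention effect. It also ignores hospital.

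The text gives the verb of comparison to these tests and gives the mixed models the task of examining cluster and period, which are nuisance terms. The only test tied by name to length of stay is the t-test used for sample size. A literal reader could take that t-test as the primary analysis and use chi-square tests for mortality and readmission.

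At stake is the validity of the primary p-value. The two routes also differ in apparent power, and the unadjusted one looks stronger. If the choice is left open, it can be made after the results are known.

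**Working it through.** **Inputs from the Sample size calculation section.** Control stay "with a mean of 8.34 days (SD ± 10.32"); "targeting a mean length of stay of 5.56 days (SD ± 10.32) after intervention"; "With a significance level of 5%, test power of 80%, and effect size of 0.27"; 5 hospitals, 6 periods of 2 months, 16 patients per hospital-period; 480 patients, 240 per group; ICC 0.001.

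**Assumed.** One hospital crosses at each step (the schedule figures are not shown); the excluded training month is ignored; secular falls of 1, 2 and 3 days per year; alternative ICCs of 0.01 and 0.05. The article gives no trend figure.

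**1. The plan's own number.** Difference = 8.34 − 5.56 = 2.78 days; d = 2.78/10.32 = 0.269. The exact two-sided t-test at 5% and 80% power needs 218 per group, 436 in all, and 436 × 1.10 ≈ 480. The stated figures reproduce.

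**2. Calendar gap between groups.** Hospitals in control per period: 5, 4, 3, 2, 1, 0. In intervention: 0, 1, 2, 3, 4, 5. That is 15 cells × 16 = 240 patients each, matching the stated split.

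- Mean control period = (1×5 + 2×4 + 3×3 + 4×2 + 5×1)/15 = 35/15 = 2.33
- Mean intervention period = (2×1 + 3×2 + 4×3 + 5×4 + 6×5)/15 = 70/15 = 4.67
- Gap = 2.33 periods × 2 months = 4.67 months

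**3. Bias and type I error of the unadjusted t-test with no true effect.** Bias = trend × 4.67/12. Standard error = 10.32 × √(2/240) = 0.942 days. Type I error ≈ Φ(bias/SE − 1.96) + Φ(−bias/SE − 1.96).

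| Assumed fall per year | False difference | Share of 2.78 days | Bias/SE | Type I error |
|---|---|---|---|---|
| 1 day | 0.39 days | 14% | 0.41 | 7.0% |
| 2 days | 0.78 days | 28% | 0.83 | 13.1% |
| 3 days | 1.17 days | 42% | 1.24 | 23.6% |

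Simulation of the same layout gave about 7%, 14% and 22–24%.

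**4. The same check with the planned adjustment.** A least-squares fit with hospital and fixed period terms, to data with a 1-day linear fall across the six periods and no intervention effect, returns an effect of 0.00 days. The unadjusted difference in that case is 2.33 × 0.2 = 0.47 days.

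**5. Clustering alone, no trend.** From first to last to cross, the hospitals contribute 1 to 5 control cells and 5 to 1 intervention cells. The hospital effects therefore enter the difference with weights 4/15, 2/15, 0, −2/15, −4/15, whose squares sum to 40/225. The true variance relative to the one the t-test assumes is [(1 − ICC) × 2/240 + ICC × 40/225]/(2/240).

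| ICC | Variance ratio | Type I error |
|---|---|---|
| 0.001 (stated) | 1.02 | 5.2% |
| 0.01 (assumed) | 1.20 | 7.4% |
| 0.05 (assumed) | 2.02 | 16.8% |

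**6. Power of the two routes for 2.78 days at 480 patients (normal approximation).**

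- Unadjusted t-test: Φ(2.78/0.942 − 1.96) = Φ(0.99) = 84%.
- Mixed model with fixed period and random hospital effects, ICC 0.001: the generalised-least-squares standard error for this layout is 1.314 days, so Φ(2.78/1.314 − 1.96) = Φ(0.16) = 56%.

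**The case against.** The strongest reply is that the adjustment is already planned. The mixed models are justified by the stepped-wedge design itself, and the fixed period effects are stated to be there for secular trends. One adjusts for a trend in order to estimate something else, and the natural candidate is the intervention effect. The sentence on simple tests speaks of variables, not outcomes, and is followed by one on descriptive presentation. It may be ordinary boilerplate. The confirmatory estimator is also something that a statistical analysis plan, not shown here, commonly settles.

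Much of this stands. A reader might infer that the trial will count any secular fall in stay as an intervention effect. The article does not support that: models that remove the trend are planned, and bias follows only if the simple tests are used for efficacy. A reader might also infer that mortality and readmission are assigned to chi-square tests; no sentence says so. Nor does clustering do visible harm on the plan's own ICC, where the t-test's error rate stays near 5%. The larger figures need ICCs 10 or 50 times the stated one.

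What does not stand is that nothing is left. The article is not silent on comparing. It names tests, does not restrict them, and gives the models a different stated purpose. The sentence on period effects governs models and cannot repair tests that are not models. This is a rule fixed badly, not a detail deferred.

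**Conclusion.** The point holds as an ambiguity with consequences. Two routes to the primary comparison are open, and the one named for comparing is confounded with calendar time. If it were used, the error would range from slight to serious depending on the trend: a false difference of 0.39 to 1.17 days and a type I error of about 7% to 22–24% for assumed falls of 1 to 3 days per year. These figures rest on one hospital crossing per period and on trend sizes that the article does not give. The direction of the problem does not depend on them, because intervention patients come later in any stepped wedge. Time confounding is the substance; clustering is negligible at the stated ICC. The planned model, if its treatment term is the test, removes the linear trend bias entirely.

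**What to change.** State in the Statistical analysis section, and in the analysis plan if one exists, that the confirmatory test of postoperative length of stay is the treatment coefficient from the already planned mixed model with fixed period and random hospital effects. Use the same structure, with a link suited to each outcome, for the between-group secondary outcomes: morbidity, mortality, readmission, PROMs and PREMs. Limit the chi-square, t and Kruskal-Wallis tests to descriptive tables.

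The cost is wording only. The models are already planned and, by the article's account, recruitment is still under way, so the change can precede the analysis. The downside should be acknowledged: for 2.78 days at 480 patients and ICC 0.001, power is about 56% by the model against about 84% by the unadjusted t-test. The higher figure comes from ignoring the period adjustment that the plan itself requires, so it is no reason to keep the unadjusted test.
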